**9) Data Management**

Data storage

Adverse events will be documented in individual case report files for each child. They will be recorded under two headings, local and general. There will be separate sections for concomitant medication, concomitant vaccination, non-serious adverse event documentation, serious adverse event documentation and study conclusion. Any deviations from the study protocol will be documented. Case report files will be kept securely.

Data will be entered in the CRFs in one of 3 ways. Data from clinic visits including screening, day 7 post vaccination follow up and medical assessments for fever will be entered directly in the CRFs carried to the dispensary on that day. Data acquired during home visits from days 1-3 post vaccination or surveillance for malaria will be entered on record sheets carried by fieldworkers. These will be transcribed to the CRFs on return from the field. Data from blood films will be transcribed to the CRF by the investigator.

Data management and analysis

Data entered into CRFs will be entered into a Visual Fox Pro™ data base as it is acquired. CRFs will be given to data entry personnel on return from the field after clinic visits. The forms generated by laboratory results and field trips will be supplied to them, after data is transcribed to the CRF by field workers or the investigators. This data base will contain the screening, post vaccination visits and surveillance, but not which vaccine was given. At the completion of the trial the code will be broken for analysis.

Analyses will be performed on subjects with intent to treat (ITT) and according to protocol (ATP).

***Intent-to-treat cohort (ITT)***

The intent-to-treat cohort will include all subjects enrolled in the study, who received at least one dose of the candidate malaria vaccines or comparator and for whom data for the observation in question are available.

***Protocol-defined cohort for analysis of efficacy (ATP)***

The protocol-defined cohort for analysis of efficacy will include all evaluable subjects (i.e., those meeting all eligibility criteria, complying with the procedures defined in the protocol, for whom data concerning efficacy endpoint measures are available.

***Safety data.***

All reactogenicity analyses will be on an intent to treat basis, comparing control to malaria vaccine. ALT, plasma creatinine, haemoglobin, white cell count, platelet values will be described by time and vaccine group.

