**2) Investigators**

[name] (PI)

[name]

[name]

[name]

[name]

[name]

[name]

[name]

(Kenya Medical Research Institute, Centre for Geographic Medicine Research – Coast)

[name]

[name]

[name]

(Nuffield Dept. of Clinical Medicine, University of Oxford)

3) Abstract

About 1 million people die each year from malaria and there is no vaccine near to licensure. The Oxford group uses a heterologous prime-boost strategy, using sequential immunisation with different vectors delivering a common antigen (ME-TRAP: multiple pre-erythrocytic stage epitopes and the whole pre-erythrocytic stage antigen TRAP). Malaria challenge studies with sporozoites from *P. falciparum*-infected mosquitoes have been used to evaluate these vaccines: some individuals have been fully protected and many immunized groups show mean delays in time to parasitaemia of about 2 days corresponding to a killing of about 90% of malaria parasites in the liver. We have found these vaccines to be safe and immunogenic among adults and children in Kenya.

This study will evaluate the efficacy of the regime of FP9:ME-TRAP (attenuated Fowlpox virus recombinant for ME-TRAP) followed by MVA:ME-TRAP (modified Vaccinia Ankara recombinant for ME-TRAP) in 1-6 year old children in Kilifi District, Kenya, during two 3-4 month surveillance periods spanning the malaria transmission seasons.The trial will be randomised and double blind, using rabies vaccine as control. We will screen 450 children, aiming to recruit 410 children to be randomised in a 1:1 ratio to active or control vaccinations. Safety and immunogenicity data will be evaluated by clinical assessments and blood tests. Subsequent weekly follow up will allow blood film examinations for all febrile children. Rates of development of febrile malaria and proportions of children with episodes of febrile malaria will be compared between groups to determine efficacy.

**4) Introduction** (see appendix for abbreviations used)

Background

Research on T cell mediated protection against malaria has been in progress for several years in the Gambia and Kilifi, Kenya, supported by Oxford University, the Wellcome Trust and others. This has progressed from studies on naturally acquired immunity to experimental vaccination; Phase 1 trials in Oxford, the Gambia and Kilifi. We now propose an immunogenicity and efficacy trial.

*Sporozoite immunization*

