MVA is much safer than vaccinia because it fails to replicate in vivo. During the smallpox eradication campaign vaccinia scarification was associated with significant side effects. The most comprehensive data come from a 10 state survey of the USA in 1968: there were 2.8 cases of post-vaccinial encephalitis, 0.9 cases of progressive vaccinia, 10.4 cases of eczema vaccinatum, 23.4 cases of generalised vaccinia and 25.4 cases of accidental infection per million primary vaccinations with non-attenuated vaccinia18. In an attempt to reduce these side effects several attenuated strains of vaccinia were developed. The most widely used of these was MVA, derived by multiple serial passage of vaccinia strain Ankara through chick embryo fibroblasts. MVA caused no serious side effects when given by intramuscular, subcutaneous and intradermal routes to 120,000 individuals in southern Germany and Turkey 19. MVA was safe when administered to neonatal mice by intracerebral and intraperitoneal routes, and did not disseminate in mice immunosuppressed by irradiation 20. It appears to be attenuated as a consequence of genetic deletions, with a unique cytokine receptor profile which may explain it’s immunogenicity and safety.

The safety data acquired during 100 immunisations with prime boost regimes in healthy volunteers in Oxford, over 200 immunisations with MVA in the Gambia and 29 adults in Kilifi, Kenya has been favourable 16,21-23. Local reactions occurred in 70% of subjects, limited to discolouration, blistering and itching, typically resolving over one week. 25% had a mild flu-like illness for not more than 24 hours after the first dose of MVA. These side effects are attenuated if MVA is given after FP9. Stocks of MVA encoding ME-TRAP are produced to GMP standard by Impfstoffwerk Dessau-Tornau, Roslau, Germany.

*Attenuated Fowlpox (FP9)*

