A nurse will be employed to give vaccinations, separate from the investigators. Standard nursing training in Kenya includes considerable emphasis on correctly giving intradermal injections, because of the importance of the BCG programme, and a practical assessment is conducted in final exams. The nurses involved in this study will be required to show they have maintained the skill of giving these vaccinations recently. They will be briefed by the local safety monitor in the importance of maintaining blinding to the investigators. They will be shown the storage arrangements for vaccine, and the doses explained. A detailed SOP will cover this area. The investigator will inform the local safety monitor of the immunisations planned each day, who will instruct the nurses which immunisations these children are allocated to give. On the morning of each immunisation day, they will remove the required vaccines, placing them in a sealed box containing ice, for transport to the field.

Immunisation will be conducted in a designated room, and the investigators will not be present during immunisation. Nurses will document the precise details of immunisation (vaccine, number of injection sites, volume administered, vial and lot number) in folders separate to the main folder held by the investigators. They will only record that immunisations have been given in the main CRF. The vaccination records will be shown to the local safety monitor on return, to ensure no incorrect immunisations have been given, and stored in a locked cabinet not accessible by the investigators.

*Storage and administration*

The vaccines will be shipped from Oxford on dry ice then stored at –700C at the CGMR-C unit until required. Vaccines will be thawed on the morning of use, and kept in a cold box in the field. They will be used within 4 hours of thawing in the field. Should vaccines not be used during the day, they may be refrigerated overnight, but not re-frozen, and used the following morning.

Temperature checks and a systematic enquiry for symptoms will be made before each vaccination. Vaccination will be deferred in any child with a clinical illness (defined as signs of obvious clinical disease and/or a fever >37.5C) on the day of vaccination. Medical treatment will be provided, including inpatient care if necessary.

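### Reactogenicity is fixed on an intent-to-treat basis with no grouping by vaccine received; harmless unless a wrong vaccine is given, but cheap to put right

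*Protocol*

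**What the plan says.** All references are to the protocol; the analysis plan is not at hand.

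- Section 9, Safety data, sets the basis: "All reactogenicity analyses will be on an intent to treat basis, comparing control to malaria vaccine". It names no other basis for reactogenicity. For the laboratory measurements it says only that "platelet values will be described by time and vaccine group", without saying whether the group is the one assigned or the one received.
- Section 9, Intent-to-treat cohort, covers enrolled children "who received at least one dose of the candidate malaria vaccines or comparator and for whom data for the observation in question are available". This settles who is included, not under which vaccine each child is counted.
- Section 8, Vaccine administration (Randomisation), provides the data needed for grouping by receipt: "Nurses will document the precise details of immunisation (vaccine, number of injection sites, volume administered, vial and lot number". The local safety monitor sees these records when the nurses return, "to ensure no incorrect immunisations have been given".
- Section 7 makes the comparison of local and systemic side effects between the two vaccine groups a specific objective.

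**The concern.** Keeping children in their assigned arm is the cautious choice for efficacy, because misallocation pulls the estimate towards no effect. For safety the same pull works the other way. A reaction to FP9 or MVA in a child assigned to rabies vaccine would raise the control rate. A child assigned to malaria vaccine who received rabies vaccine would tend to lower the malaria-vaccine rate. Either error would make the candidate look better tolerated than it is.

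The monitor's review of the records follows the day's injections. It can find an error and prevent a repeat, but it cannot undo the dose. If an error did occur, the stated basis would place the child in the less informative column even though the record shows what was given. The Data Safety Monitoring Board paragraph plans no interim report and has the board receive a safety and reactogenicity summary after the trial, so this table would be the main planned between-group safety comparison.

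**Working it through.** The protocol gives no figure on this point, so there is nothing to reproduce. The check asks how far as-randomised grouping could move the result.

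**Inputs**
- Arm size: the abstract (section 3) has the trial "aiming to recruit 410 children to be randomised in a 1:1 ratio to active or control vaccinations", so 410 / 2 = 205 per arm.
- Malaria-vaccine reaction rates: section 4, on MVA, says "Local reactions occurred in 70% of subjects" and gives 25% for a mild flu-like illness. Both come from adults.
- Control reaction rate: not given. Assumed 10%; for local reactions 30% was also tried.
- Wrong-vaccine rate: not given. Assumed 0 to 20 children in each arm.

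**Formula.** Let p1 and p0 be the true rates under malaria and control vaccine, and let a fraction m of each arm receive the other vaccine. Grouped as randomised:
- malaria arm: p1(1 − m) + p0·m
- control arm: p0(1 − m) + p1·m
- difference: (1 − 2m)(p1 − p0)

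Grouped by receipt, the difference is p1 − p0.

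**Results**, with m = k/205 for k misvaccinated children in each arm. Power is for a two-sided 5% comparison of 25% with 10%.

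| k per arm | 1 − 2m | 70% v 10%: 60 points reads | 25% v 10%: 15 points reads | Power, 25% v 10% |
| --- | --- | --- | --- | --- |
| 0 | 1.000 | 60.0 | 15.0 | 98.1% |
| 1 | 0.990 | 59.4 | 14.9 | 97.9% |
| 2 | 0.980 | 58.8 | 14.7 | 97.7% |
| 4 | 0.961 | 57.7 | 14.4 | 97.2% |
| 10 | 0.902 | 54.1 | 13.5 | 95.3% |
| 20 | 0.805 | 48.3 | 12.1 | 89.9% |

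For 70% against 10% or 30%, power stays at about 100% in every row. If errors run one way only (control children given malaria vaccine), the factor is 1 − m: one such child turns 60.0 points into 60 × (1 − 1/205) = 59.7.

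**Rare event.** Suppose there is one severe reaction, in a control-assigned child who was given malaria vaccine, and no other wrong dose. By receipt the rates are 1/206 = 0.49% for malaria vaccine and 0/204 for control. As randomised they are 0/205 and 1/205 = 0.49%. The size is the same but the sign is reversed. This is the one setting in which the grouping changes what the table says.

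**The case against.** The strongest reply is that the protocol uses intent to treat as an inclusion label. Its cohort consists of children who "received at least one dose of the candidate malaria vaccines or comparator", set against a compliant according-to-protocol cohort, and section 8 keeps incompletely immunised children in the safety assessment. On that reading the Safety data sentence says only that all dosed children are counted. This stands in part: the protocol does not spell out that a wrongly vaccinated child counts under the vaccine not received. But it does not say the opposite either, and without a different definition the ordinary as-randomised meaning applies. A later analysis plan could set the grouping, but it would have to interpret or depart from a sentence that covers all reactogenicity analyses.

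A reader might infer that wrong doses are expected. The documents do not support that. The monitor's review is a safeguard and no error rate is given. There are others: a dedicated nurse, a detailed SOP, daily instructions from the local safety monitor, identification by name, parent's name, age and photograph, and documentation of deviations.

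The rare-event case is also softened. Serious events go to the local safety monitor and the board for individual assessment, and the monitor holds code-break envelopes and sees the vaccination records. The 70% input probably overstates the difference in these children: section 4 says MVA side effects are attenuated after FP9 and reports minimal reactogenicity in children so far.

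A reader might also object that one contrast spans two vectors. Nothing in the Safety data paragraph prevents tables by dose; that is layout for the analysis plan.

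**Conclusion.** The point holds as a low-severity improvement. The protocol fixes intent to treat for all reactogenicity analyses and does not provide for grouping by vaccine received, which is the better basis for a safety table.

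It would be tempting to say that the safety difference is understated. The documents do not support that, because any distortion depends on a wrong vaccine actually being given. With no errors the two groupings are identical. One or two misvaccinated children per arm cost about 1–2% of the difference and four cost about 4%, with little loss of power. The larger rows in the table have no basis in the documents and only show the trend. The practical exposure is a severe reaction rare enough for one child to decide the direction of the comparison.

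These sizes rest on 205 children per arm, errors spread evenly between arms, adult reaction rates and assumed control rates. The factor 1 − 2m itself depends only on the even spread.

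**What to change.** In section 9, Safety data, replace the intent-to-treat basis with a statement that reactogenicity and laboratory safety values are tabulated by the vaccine actually received, taken from the nurses' vaccination record, among all children with at least one dose. Keep the as-randomised table beside it as a check. The analysis plan can settle how a child who received both vaccines is classed.

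The cost is one sentence and a merge of the vaccination records when the code is broken. No new data are collected, blinding during the trial is unaffected, and the efficacy analyses stay as they are. The one drawback is that, if errors occur, the as-received groups are no longer strictly the randomised ones; the retained table covers that.

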***Immunogenicity***

Both ITT and ATP cohorts will be analysed, using both immediate *ex vivo* and cultured ELISpots. Immunogenicity will be examined by age, sex, presence of stool helminth infection and parasitaemia at screening. Geometric means of T cell numbers with 95% confidence intervals for central tendancy will describe groups.

*Demographic data.*

Age, sex and bed net use will be presented by treatment group to ensure comparability.

*Efficacy*

Efficacy will be analysed by both ITT and ATP.

Primary Analysis

Cox regression model analysis of incidence of clinical disease will allow assessment of the time to first episode as the primary outcome. Clinical disease will be defined by fever and parasitaemia above a threshold defined from logistic modelling of the risk of fever for parasite densities. Age, bed net use, blood stage immunity, sickle cell status and thalasaemia typing will be used as covarietes. It will also allow correlation of immune responses with protective efficacy.

Secondary analyses

- The total number of clinical disease episodes during surveillance, using age, bed net use and blood stage immunity as covarietes.
- the number of febrile malaria episodes in vaccine versus control groups, as calculated by the Malaria Attributable Fever Fraction, corrected by number of children and time of observation. This method does not assign a definitive status to each child, but produces a figure for the fraction of the group estimated to have febrile malaria. The cross-sectional bleed will be used to fit the model by providing the afebrile population, but will not be used in determining the Malaria Attributable Fever Fraction. The first half and second half of monitoring will be analysed separately.
- the other secondary analyses will compare mean haemoglobin concentrations during cross-sectional surveys, and the number of high parasitaemia (>500,000 per microlitre) infections in each group. The incidence of severe malaria will not be frequent enough to allow analysis, but data will be presented.

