We wish to undertake a more detailed study of the T cell response to vaccination in order to establish the further correlates of immunity, and whether T regulatory responses are seen in young children in a malaria endemic area and reduce the immunogenicity of vaccination.

Such studies will inform further vaccine design and development.

*Potential subjects with HIV*

The need for an HIV test before immunisation would preclude widespread delivery of a successful immunisation, and it is clearly desirable to protect HIV infected individuals as well as uninfected. These highly attenuated vectors are unable to replicate in human cells, and are very likely to be safe in HIV: this is confirmed by safety data for these vectors for adults in Germany 43 and New York 44. We have immunised 3 adults with HIV infection in Kilifi, and plan to immunise at least 3 more over the next few months. (SSC proposal no. 759). We therefore propose to not include HIV testing as part of the health screen for prospective volunteers. This is likely to result in immunising 3-4 HIV positive children, and should not affect efficacy results.

*Subjects with asymptomatic malaria parasitaemia or helminth infection at immunisation*

Asymptomatic parasitaemia is common in the population eligible for preventative malaria vaccines. Previous studies have used antimalarials prior to each vaccine dose 45,46, because of concerns about immunogenicity. However, others have compared parasitaemic and aparasitaemic children, and suggested greater efficacy in the children with parasitaemia47. There is also data that T cell responses to immunisation with tetanus toxoid 48-50 and BCG 51 may be reduced by symptomless helminth infections. Certainly, it would be impractical to clear either parasitaemia or intestinal worm infections from children a prior to vaccination on a large scale, and an important component of this trial will be to examine whether parasitaemia or helminth infection at screening has an impact on immunogenicity.

*Outcome measures*

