**8) Design**

Study site

The investigation will take place at the KEMRI Centre for Geographic Medicine Research – Coast, Kilifi. There are several dispensaries suitable for such a study in Kilifi district. We currently plan to use Gongoni dispensary, 30km south of KEMRI Centre for Geographic Medicine Research. Kilifi District experiences long rains in May-July and short rains in November/December. Gongoni is near a fresh water lake, and this may explain the continued presentation of malaria cases to Gongoni dispensary when other areas have little malaria. Measured Entomological Inoculation Rates in the area vary from 10-50 per year. The dispensary is the primary source of antimalarial treatment in the area: there are very few shops or private dispensaries in the area. The local administrative structure involves an area chief, a sublocation chief, a dispensary health committee and a clinical officer based in the dispensary. All these parties are keen to facilitate interventional research in the area. Adequate space exists in the dispensary to see children for clinic visits and immunisations.

Study population

There are 600 children between the ages of 1 and 6 years within a 2 kilometre radius of the dispensary. The local population are predominantly Mijikenda (Giriama), and subsistence farmers.

Sampling

A sample size calculation using a time to event, and assuming an even distribution of the risk of malaria, is based on a 60% risk of clinical disease during the first rainy season (estimate from previous studies in the area). To detect 40% efficacy with 90% power at p=0.05 requires 340 children in total, allowing for 30% probability of loss to follow up (spread over the period of monitoring) requires 372 children. To accommodate early loss to follow up, and incomplete immunisations, we aim to recruit 410 children, which we estimate will require 450 children to be screened for eligibility. Should the proportion of children with malaria attributable fever be only 40% because of poor rainfall, we would still have 90% power to detect 48% efficacy.

Sensitisation and recruitment

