- *Ex vivo* ELISpot (to count IFN gamma producing T cells) and cultured ELISpot.
- Where possible, lymphocytes will be frozen for repetition of unusual results, or to explore specificity of responses with peptide pools, or after depletion of specific cell populations.
- Plasma stored to assay antibodies to TRAP or viral vectors.
- The pelleted red cell and neutrophils after PBMC isolation will be used for sickle cell and thalasaemia typing (electrophoresis and PCR typing respectively)
- Stool microscopy for helminths

Blood will be drawn into a paediatric size EDTA tube, and a glass lithium heparin tube. These tests will require 5 mls.

*Parasitaemia at screening*

Children with parasitaemia will not be excluded from study. It is unclear whether chronic parasitisation would be helpful or unhelpful in immunogenicity: other vaccine studies have suggested that clearing parasitaemia might reduce the observed immunogenicity 47. In the absence of clear evidence, we would not clear parasitaemia during the first two immunisations. Children with symptoms or signs at screening and parasitaemia will be treated. All children will be followed up closely during immunisation, including those with asymptomatic parasitaemia, and treatment given should they develop symptoms. Antimalarial treatment will be given to all children after the third immunisation to prevent chronic parasitaemia complicating the surveillance period. Similarly, children with signs or symptoms due to helminth infection confirmed by stool microscopy will be treated immediately. Those without will be treated after the immunisation is completed.

*Anaemia at screening.*

Children identified with anaemia (Haemoglobin less than 8.0 g/dl) will receive iron supplementation, and further standard investigation and management. If they have no clinically significant signs or symptoms on screening, they will still be eligible to enter the study.

*Laboratory procedure.*

Full blood counts will be performed on the EDTA anticoagulated blood. The lithium heparin tube will be centrifuged, and 1 ml plasma removed for biochemistry and storage. 1 ml RPMI will be added to the remaining blood, and PBMC separated by standard techniques. At screening, 1ml of the pelleted red cells and neutrophils will be taken for PCR and electrophoresis typing for thalasaemia and HbS respectively.

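### The covariate list of the primary Cox model leaves out parasitaemia at screening, a pre-randomisation variable that could be added at almost no cost for a modest gain in precision

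*Protocol*

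**What the plan says.** Section 9 (Efficacy, Primary Analysis) makes time to first clinical episode the primary outcome, analysed by Cox regression. It fixes the adjustment set: "Age, bed net use, blood stage immunity, sickle cell status and thalasaemia typing will be used as covarietes". The secondary analysis of total episodes uses age, bed net use and blood stage immunity.

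Parasitaemia at screening appears elsewhere in the protocol:

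- Section 9, Immunogenicity: "Immunogenicity will be examined by age, sex, presence of stool helminth infection and parasitaemia at screening".
- Section 8, Parasitaemia at screening: "Children with parasitaemia will not be excluded from study". The same paragraph provides for antimalarial treatment of every child after the third dose, so that chronic infection does not complicate surveillance.
- Section 4, on asymptomatic parasitaemia at immunisation: "others have compared parasitaemic and aparasitaemic children, and suggested greater efficacy in the children with parasitaemia".

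Under Randomisation in section 8, the list of children is sorted by age and sex before the block allocation is applied. The planned comparability table in section 9 covers age, sex and bed net use.

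The sample size in section 8 (Sampling) "is based on a 60% risk of clinical disease during the first rainy season" and assumes that all children share the same malaria risk. The basic requirement is stated as follows: "To detect 40% efficacy with 90% power at p=0.05 requires 340 children in total". A 30% loss accruing during monitoring raises the total to 372. A further margin for early dropout and unfinished courses leads to the target: "we aim to recruit 410 children".

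**The concern.** The protocol treats infection status at screening as relevant to how a child responds to the vaccine, enrols infected children, and names the variable for one analysis. It leaves it out of the efficacy model. Infection at screening may mark a child's exposure, and treatment that clears the parasites does not change where the child lives. Antibody-based blood stage immunity is related but is not the same measurement, and the laboratory section gives no timepoint for those antibodies.

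If the variable does predict later febrile malaria, omitting it from a Cox model has two consequences. The estimated hazard ratio moves slightly towards 1 and some power is lost. In addition, a chance difference in prevalence between arms would be neither shown nor adjusted for.

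**Working it through.** **1. Reproduce the protocol's figures.** Inputs from section 8, Sampling: control risk 0.60, efficacy 40% (hazard ratio 0.60), 90% power, p = 0.05 taken as two-sided.

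- Vaccine-arm risk: 1 − 0.4^0.6 = 0.423. Mean risk: (0.600 + 0.423)/2 = 0.511.
- Freedman: events = (1.96 + 1.2816)² × (1.6/0.4)² = 10.51 × 16, giving 169. N = 169/0.511 = 330, within 3% of the stated 340.
- Schoenfeld: events = 4 × 10.51/(ln 0.6)², giving 162. N = 317 without loss.
- With exponential loss reaching 30% by the end of follow-up, the event probabilities are 0.518 (control) and 0.361 (vaccine), mean 0.440. Schoenfeld then gives 162/0.440 = 368, against the stated 372.

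The stated sizes hold under the protocol's assumption of even risk.

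**2. Cost of omitting the covariate.** Prevalence and hazard ratio (HR) of screening parasitaemia are assumptions; the documents give neither. Event times were simulated as exponential with a true conditional treatment hazard ratio of 0.60, the baseline hazard set so that overall control risk is 60%, and 30% loss spread over follow-up. Cox models were fitted without and with the binary covariate, with no other covariates. There were 2,500 runs per row; the standard error of each power is about √(0.9 × 0.1/2500) = 0.6 points.

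| Prevalence, HR | Estimated treatment HR, N = 372: omitted / added | Power, N = 372: omitted / added | Power, N = 410: omitted / added |
| --- | --- | --- | --- |
| 20%, 1.5 | 0.602 / 0.599 | 89.6% / 90.0% | 92.6% / 93.0% |
| 20%, 2 | 0.607 / 0.597 | 89.4% / 90.6% | 92.3% / 92.8% |
| 30%, 2 | 0.612 / 0.601 | 87.5% / 89.8% | 90.7% / 92.6% |
| 30%, 3 | 0.629 / 0.600 | 84.5% / 89.8% | 88.0% / 93.0% |
| 50%, 4 | 0.645 / 0.602 | 80.7% / 90.9% | 86.4% / 93.8% |

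At N = 372 the loss is 0.4 to 2.3 points for an HR of 1.5 to 2, and 5.3 points at 30% prevalence and an HR of 3. At an HR of 2, efficacy reads about 39% instead of 40%.

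**3. With a covariate already in the model.** A prognostic score standing for age and immunity (HR 1.5 per standard deviation, correlation 0.5 with the liability to parasitaemia, prevalence 30%) was adjusted for throughout. Power at N = 372, omitted / added: 88.2% / 90.4% at an HR of 2, and 85.4% / 90.8% at an HR of 3. At N = 410: 90.6% / 92.6% and 89.0% / 94.1%. In this configuration the gain from adding parasitaemia is about the same as in step 2. A closer correlation would leave less to gain.

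**4. Chance imbalance.** Section 8 (Day 7/Week 12 and end of study follow up) mentions 380 immunised children, about 190 per arm. At 30% prevalence, the standard deviation of the difference between arms is √(2 × 0.3 × 0.7/190) = 0.047. A difference of 1.96 × 0.047 = 9.2 points or more, in either direction, arises in about 1 trial in 20. With an HR of 2 it shifts the log hazard ratio by about 0.092 × ln 2 = 0.064, so an estimate near 0.61 becomes 0.61 × e^0.064 = 0.65 or 0.61 × e^−0.064 = 0.57 (efficacy 35% or 43%). Simulation at N = 380 agrees. In the unfavourable direction power is 79% without the covariate and 91% with it, and with it the estimate stays at 0.60.

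**The case against.** The strongest reply is that nothing here is an error. The protocol pre-specifies five sensible covariates, and a sixth is a preference. It also mentions a separate reporting and analysis plan, which could refine the list. Every child is treated after the third dose, and screening (February to March) precedes surveillance (from mid-May) by about two months or more, so earlier infection status need not be strongly prognostic. Age, bed net use and blood stage immunity carry some of the same information. All of this limits the likely gain, and none of it shows harm from adding the variable.

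Three stronger readings are tempting, and the documents do not support them:

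- *That the efficacy estimate is biased.* Treatment is randomised, so there is no confounding and the test of no effect is valid. The shift towards 1 is non-collapsibility: the model estimates an effect averaged over infection status.
- *That the 90% power is lost if infection status predicts malaria.* The stated power assumes equal risk and no covariates, so it never relied on this variable. In the step 2 scenarios with an HR of 2 or less it stays above 90% with 410 children and within 2.5 points of 90% with 372. A clear shortfall needs an HR of about 3 or more and a common exposure, for which the documents offer no evidence.
- *That the protocol contradicts itself by using the variable only for immunogenicity.* The introduction gives that as its purpose. Its remark about greater efficacy in parasitaemic children concerns effect modification, which a main-effect covariate would not address.

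**Conclusion.** The point holds as an optional improvement. The primary model omits a pre-randomisation variable that the trial already uses and does not balance by design. If that variable is prognostic, leaving it out costs about 0.5 to 2.5 points of power at an HR of 1.5 to 2, and about 5 points at an HR of 3 with 30% prevalence. It also leaves any chance imbalance uncorrected. These sizes rest on assumed prevalence and prognostic strength, and on an effective sample between 372 and 410, since the larger figure is meant to absorb early losses. If infection status turns out not to be prognostic, nothing is lost by its absence and next to nothing by its inclusion.

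**What to change.** Before unblinding, add parasitaemia at screening (yes/no) to the covariates of the primary Cox model and of the total-episodes analysis, and show it by arm in the baseline table. Use yes/no status, because a screening parasite density is not a promised measurement. Screening status itself is implied by the immunogenicity analysis and by the paragraph on parasitaemia at screening, but the listed screening tests do not name a blood film, so confirm that it is recorded for every child.

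The cost is one line of analysis text, one row in a table and one degree of freedom. Made after unblinding, the same change would look data-driven.
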